The present research project aims to compare the effect of the above tested oral health care package versus routine dental care advice generally imparted by the AWWs on change in dental caries, gingival health and S mutans levels among 1 to 6-year-old children and KAP regarding oral health among their mothers at AWCs. The study shall be simultaneously carried out at two geographically distant sites; peri-urban areas of Chandigarh and rural parts of Cuttack, Orissa. In contrast to Chandigarh, rural Cuttack has got a significant proportion of the tribal population with differing socio-economic, cultural background and dietary habits etc. Keeping two sites in the study shall also additionally permit comparison of study outcomes between these two different populations [16, 17].

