## Methods

### Study design

This will be a pragmatic, two-arm, parallel-group, community-based controlled trial with clusters of AWCs within ICDS blocks as the unit of allocation. Two geographically distant ICDS blocks will be selected at each of the study sites, viz. Chandigarh and Cuttack. The selected blocks will be randomly allocated to the intervention and control group using sealed envelopes by a statistician who will not be the part of this study. AWCs under each of the two selected blocks shall be enumerated and, from them, one AWC will be randomly selected, and further AWCs located adjacent to this AWC will then be chosen so that a cluster of AWCs is formed within the block. This cluster of AWCs will constitute a unit of allocation. A typical cluster-randomised controlled trial should have a large number of small-sized clusters, randomly allocated to an intervention and control arm. However, for logistic reasons, we have opted for a pragmatic design in which only two large-sized clusters at each study centre (Chandigarh and Cuttack) would be compared.

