### Sample size estimation

Sample size calculation for the study has been based upon a similar study conducted by Lawrence HP et al., 2008 for prevention of dental caries among aboriginal children in Canada, with 2-year, follow up [18]. In the above study, the mean (SD) change of dmfs in intervention and control arm was 11 (14.3) and 13.47 (16.3), respectively, resulting in a mean difference of 2.47.

Assuming a 5% alpha error and 20% beta error, to detect a mean difference with standard deviations as above, using the sample size formula (z_1-α/2_ + z_1-β_)^2^ x (σ_1_^2^ + σ_2_^2^)/(μ_1_-μ_2_)^2^, the required sample size has been calculated to be approximately 605 in each arm. The design effect due to clustering has not been included, because we do not have prior information about the intra-class correlation within a cluster. To account for an attrition in the number of study subjects, and to account for a decrease in the effect size (due to a potential waning in the performance of AWWs in the intervention clusters over the three-year study period, and a possible Hawthorne effect) it was decided to inflate the sample size approximately 1.5 times, resulting in 950subjects in each arm at each study center (Chandigarh and Cuttack). On average, around 25 children are attached to each AWC. Therefore, at each study centre, a cluster of 40 AWCs will be selected within each of the two ICDS blocks, and the blocks will be randomly located to the intervention and the control arm.

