### Outcome variables

These will be assessed at enrollment, 6 months, 1 year, 2 years and 3 years after the start of the project. Personnel assessing the outcomes will be blinded to the group of intervention. The primary outcome variable will be change in dmfs count among 1 to 3-year-old children over a follow-up period of three years.

The secondary outcome variables will be:
individual child-level variables: dental caries count (caries reversals and caries increment), S mutans levels, Gingival and Plaque Indexmother and AWW-level variables: oral health-related KAP

Variables that will be measured at baseline and at each of the above time points are shown in Table 1.

**Table 1 Tab1:** Variables to be assessed during the study

Variables Assessment	Variable types	Data Analysis	Anticipated Outcomes	Time of measurement
At the level of the mother (Independent variables)				
Socio-Demographics	Continuous & Categorical	T-test and Chi-square tests.	Assess the distribution of population characteristics	At baseline
Health Literacy Levels	Continuous	T-test	Assess health-related literacy of the individual	At baseline
At the level of the child (Potential Confounders)				
Child Anthropometry (Weight & BMI)	Continuous	T-test	Assess BMI	At baseline and 6 months, 1 year, 2 years and 3-years post-intervention
Oral Health services utilisation	Categorical	Chi-square test	Assess the utilisation of dental care in the last 12 months	At baseline and 6 months, 1 year, 2 years and 3-years post-intervention
At the level of Mother and Anganwadi Worker (Outcomes)				
Oral Health-related KAP	Continuous & Categorical	T-test and Chi-square test	Assess the level of KAP related to oral health issues	At baseline and 6 months, 1 year 2 years and 3-years post-intervention
At the level of Child (Outcomes)				
Dental caries count	Continuous and Categorical	T-test and Chi-square test	Assess the level of dental caries status	At baseline and 6 months, 1 year and 3-years post-intervention
S. mutans levels	Continuous and Categorical	T-test and Chi-square test	Assess the level of dental caries causing organisms	At baseline and 6 months, 1 year and 3-years post-intervention
Gingival and Plaque Index	Continuous and Categorical	T-test and Chi-square test	Assess the level of oral hygiene	At baseline and 6 months, 1 year and 3-years post-intervention

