### Plan for analysis

As the population of children in an AWC is not stable, with older children who cross 6 years of age leaving the AWC and young children joining the AWC; two types of analysis have been planned. The primary analysis will be an inter-group comparison of a stable cohort of children aged 1 to 3 years who will be recruited at the beginning of the study and shall be followed up for 3 years until the age of 4 to 6 years respectively. The secondary analysis will be a cross-sectional inter-group comparison of all available children aged 1 to 6 years present at follow up evaluations (6 months, 1 year, 2 year and 3 years). Children in the secondary analysis will have varying points of entry and different durations of follow-up. All the above-listed outcome variables will be analysed both in the primary and the secondary analysis.

The primary analysis will be done on an intention-to-treat basis. Qualitative data shall be expressed using frequency distribution and percentages, whereas quantitative data shall be expressed as mean (standard deviation) or median (1st, 3rd quartile) depending upon distribution. Normality of distribution will be assessed by Shapiro Wilk test and Q-Q plot. Qualitative variables will be compared between the two groups by chi-square test or Fisher’s exact test, as appropriate. Quantitative variables will be compared between the two groups by Student’s t-test or Mann-Whitney U test, depending upon distribution. Repeated measures analysis between the two groups will be performed using two-way repeated-measures ANOVA or mixed linear models or generalised estimating equations, depending upon the variable and statistical assumptions.

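### Four block-level clusters are allocated, but the stated tests treat children as independent, so p-values, and any intervals on the same standard errors, are too optimistic

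*Protocol article*

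**What the plan says.** **Allocation.** Protocol article, Study design: "The selected blocks will be randomly allocated to the intervention and control group using sealed envelopes by a statistician". A cluster of adjacent AWCs within a block is named as the unit of allocation. The section accepts that a cluster trial normally has many small clusters, but says that for logistic reasons "only two large-sized clusters at each study centre (Chandigarh and Cuttack) would be compared". Sample size estimation adds that "a cluster of 40 AWCs will be selected within each of the two ICDS blocks", with about 25 children per AWC.

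**Analysis.** Plan for analysis: "Quantitative variables will be compared between the two groups by Student’s t-test or Mann-Whitney U test, depending upon distribution". Categorical variables get a chi-square or Fisher's exact test. Table 1 under Outcome variables lists "T-test and Chi-square test" for dental caries count, *S. mutans* levels and the gingival and plaque indices. Two-way repeated-measures ANOVA, mixed linear models and GEE are alternatives for repeated-measures analysis. No section names AWC, block or site as a random effect, clustering unit or stratum.

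**Sites.** Background: "Keeping two sites in the study shall also additionally permit comparison of study outcomes between these two different populations".

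**The concern.** The unit that is allocated and the unit that is analysed do not match. A t-test, Mann-Whitney, chi-square or Fisher's exact test takes every child as an independent observation. Children at one AWC share a worker, and children in one block share diet, water and access to care. Their outcomes are therefore likely to be correlated, and a child-level standard error omits that correlation.

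The blocks are deliberately far apart to avoid contamination, so some difference between them without any intervention is plausible. Within a site there is one block per arm, so such a difference cannot be told apart from the effect of the package. The article foresees presenting results to policymakers and extending the programme to other AWCs, so a spuriously small p-value on the primary outcome would matter.

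**Working it through.** **1. The plan's own figure.** Inputs from Sample size estimation: "Assuming a 5% alpha error and 20% beta error"; mean dmfs change (SD) "was 11 (14.3) and 13.47 (16.3), respectively, resulting in a mean difference of 2.47".

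n = (1.960 + 0.842)² × (14.3² + 16.3²) / 2.47² = 604.9, which is the stated 605 per arm. It reproduces only as an individually randomised, two-sided comparison. The section says that no design effect was included because the ICC is unknown. It attributes the inflation to 950 per arm per site to attrition and a smaller effect, not to clustering.

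**2. Number of allocated units.** 2 sites × 2 blocks = 4, one per arm per site. Possible allocations: 2 × 2 = 4. The smallest two-sided randomisation p-value is 2/4 = 0.5.

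**3. False-positive rate of the child-level test.** Let a and b be the shares of total variance lying between AWCs within a block and between blocks. With m children per AWC and M = 40m per block:

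DEFF = 1 + (m − 1)a + (M − 1)b

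True error of a nominal 5% test = 2 × [1 − Φ(1.96/√DEFF)]

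Assumptions, none of them in the article: m = 15 (so M = 600), a = 0.02, and the values of b. The 40 AWCs per block are from the article.

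If AWC clustering is modelled but block is not, the standard error includes only D₀ = 1 + 14 × 0.02 = 1.28, and the error is 2 × [1 − Φ(1.96 × √(1.28/DEFF))].

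| Block ICC b | DEFF | Child-level test | After AWC modelling |
|---|---|---|---|
| 0 | 1 + 0.28 = 1.28 | 8% | 5% |
| 0.001 | 1.28 + 0.599 = 1.88 | 15% | 11% |
| 0.005 | 1.28 + 2.995 = 4.28 | 34% | 28% |
| 0.01 | 1.28 + 5.99 = 7.27 | 47% | 41% |

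Simulated null trials with the same structure agree to within about 2 percentage points.

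**4. Dependence on the assumed 15 children.** With a = 0.02 and b = 0, the rate is 7%, 8% or 11% for 10, 15 or 25 children per AWC. Using the planned 950 per block and a single block-level ICC (DEFF = 1 + 949 × ICC), it is 16% at 0.001, 41% at 0.005 and 54–55% at 0.01.

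**5. Effect on an interval.** Variance = (14.3² + 16.3²)/2 = 235.1. With 1,200 children per arm pooled over sites, the child-level SE is √(2 × 235.1/1200) = 0.626, a 95% half-width of 1.23 dmfs. Multiplying by √DEFF gives 1.39 (b = 0), 1.68 (0.001), 2.54 (0.005) and 3.31 (0.01). At b = 0.005 the half-width already exceeds the design difference of 2.47, even with the normal quantile.

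**6. Information at block level.** Four block means leave 2 df (critical t 4.30), or 1 df if paired within site (critical t 12.7). At a block ICC of 0.01 with 950 per block, power for 2.47 dmfs is about 15% or 10%. The unadjusted calculation gives 94% with 950 per arm.

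**The case against.** **The design limit is disclosed.** The article says openly that it has too few clusters and no design effect. This stands as far as it goes: the coincidence of block and treatment within a site, and the minimum p of 0.5, are properties of the design that no analysis wording can remove. But disclosing a limit does not justify tests that ignore it, and the choice of tests can still be changed.

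**Mixed models and GEE are listed, and an unseen SAP may supply their structure.** This stands in part. The primary outcome is measured repeatedly, so such a model might be used for it. A reader might infer that the plan excludes these models from the primary comparison; the text does not say so. But they are offered beside repeated-measures ANOVA, which has no cluster term, and for repeated measures, not for clustering. The child-level tests are stated outright in the text and in Table 1, so this is more than a detail left open.

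**The size rests on assumptions.** This is correct. The article gives no ICC and no count of 15 children per AWC. The direction holds for any positive correlation; the percentages do not.

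**Site-specific testing.** A reader might infer that the plan tests for significance within each site. It does not specify this. The Background promises only a comparison between the two populations, which can be descriptive.

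**Conclusion.** The concern holds. The article states child-level tests that do not match its own unit of allocation. Under the assumed 15 children per AWC and AWC ICC of 0.02, the false-positive rate is about 8% with no block variance, and about 34% or 47% at a block ICC of 0.005 or 0.01. The article does not mention confidence intervals; the point extends to any interval built on the same standard errors.

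Three stronger readings are not supported:

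- **A false positive is certain.** The plan allows a block difference to be reported as an effect. How likely that is depends on correlations the article does not give.
- **Modelling AWC solves the problem.** It restores 5% only when block variance is zero, and leaves about 28% or 41% at block ICC 0.005 or 0.01. The AWCs were not the allocated units.
- **Block variance cannot be estimated at all.** Across the two sites it has 1 to 2 df, which is too few for a useful estimate but not none. Within a single site it cannot be separated from treatment.

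**What to change.** 1. Replace the child-level tests, for the primary outcome and for the other child and mother outcomes in Table 1, with one pooled model stratified by site. Use a linear model, or a suitable GLMM or GEE for categorical or skewed outcomes. Include treatment, site and, where relevant, baseline dmfs, with AWC as random effect or clustering unit.
2. State that this model handles AWC clustering only, that its p-values and intervals are conditional on the four chosen blocks, and that they are not confirmatory. Give the reasons: treatment and block coincide within a site, only 1 to 2 df exist at block level, and the smallest two-sided randomisation p is 0.5.
3. Report beside it a block-level estimate, or a sensitivity table that widens the primary interval over a stated, assumed range of block ICC, for example 0.001 to 0.01.
4. Present site-specific results descriptively.

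The cost is plan wording and modest programming, with no new data. The downside is wider intervals and a less confirmatory claim. The four-block design itself is not repaired by these changes.

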### Data monitoring, quality assurance and auditing

The real-time data entry would be done using a mobile tablet-based data collection platform. To ensure project efficiency we will have (a) well trained team of dentists and field workers (b) calibration of dentists and field workers before commencement of study, at 6 months, 1 year and 2 years (c) outcome assessors who will be blinded for all follow up examinations (d) geographical distance between the ICDS blocks to avoid contamination, (e) weekly meetings with the research staff, (f) logs of all study participant contacts. To ensure efficient and accurate data management, the electronic data collection system will centrally collect all the data on the server and have an administrative account to (i) maintain records of all the data gathered from the participants during each visit (ii) central data processing and (iii) fortnightly data checks. Security of the data will be maintained through regular backups, and all computers and specific data files will be password protected and kept in a locked file cabinet. Only the project Principal Investigator will have access to this administrative account.

Further, a Data Monitoring Committee independent of the study sponsors and headed by Principal Investigator at the Technical Co-ordinating Centre shall carefully monitor the project during its course. Adverse events if any shall be carefully looked upon, documented and reported to the relevant authorities, if that warrants any treatment shall also be taken care off. Subjects who encounter any significant adverse event shall be excluded from the trial, and a noting shall be made for the same. The committee shall also carry out periodic interim assessments to review further course of study, shall look upon any deviations required from the protocol. Committee will further submit its report to the funding agency task force, which would take the final decision on deviations from the protocol and if trial needs to be terminated at any point of time. Such deviations if any, shall be communicated to all the stakeholders including investigators from all the participating sites, funding agency, institutional ethics committee, Clinical Trials Registry, India, study participants, protocol publication journal. This funding agency task force headed by an independent external expert would carry out annual project auditing as well. At the end of the project, detailed report about project outcomes shall be reviewed by the funding agency taskforce and the outcomes may be presented to policymakers at central as well as state levels. Project results shall be disseminated through scientific research publications.

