### Study groups and intervention

#### Group I (intervention group AWC)

Oral Health Care Package (described below) for primary prevention of oral diseases will be delivered to the study participants in this group.

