#### Group II (control group AWC)

Participants will receive the standard care, i.e. the routine dental care available at the AWCs. The prevailing standard of oral health care in AWCs is part of maintaining complete hygiene of the body, wherein the AWW gives basic instructions to maintain oral hygiene too.

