#### Application of 2.26% fluoride varnish and 10% Povidone-iodine

2.26% fluoride varnish and 10% Povidone-iodine will be topically applied to the teeth of children aged 1–6 years, once every 3 months, by a dentist in the same appointment

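### The rule that excludes children from the trial after a significant adverse event is not reconciled with the intention-to-treat primary analysis

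*Protocol article*

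**What the plan says.** The exclusion rule is in the protocol article, section Data monitoring, quality assurance and auditing: "Subjects who encounter any significant adverse event shall be excluded from the trial, and a noting shall be made for the same". It covers subjects in either arm and refers to the trial as a whole, not only to the study applications. The same paragraph requires adverse events to be documented, reported and, where warranted, treated.

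The Plan for analysis defines the main comparison and its basis: "The primary analysis will be an inter-group comparison of a stable cohort of children aged 1 to 3 years", followed for three years, and "The primary analysis will be done on an intention-to-treat basis". The outcome is set under Outcome variables: "The primary outcome variable will be change in dmfs count among 1 to 3-year-old children over a follow-up period of three years".

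The arms differ in exposure. For Group I, "Oral Health Care Package (described below) for primary prevention of oral diseases will be delivered to the study participants in this group". One component of that package is that "2.26% fluoride varnish and 10% Povidone-iodine will be topically applied to the teeth of children aged 1–6 years", every three months, by a dentist. For Group II, "Participants will receive the standard care, i.e. the routine dental care available at the AWCs".

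**The concern.** Intention-to-treat keeps every allocated child in the assigned arm and calls for the outcome to be sought whatever happens after allocation. The exclusion sentence takes a child out because of something that happens after allocation. Field staff who follow it would stop examining that child. The three-year dmfs value would then never be collected, and no later analysis plan could recover it.

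Events caused by the topical agents can arise only where the agents are given, so losses from this rule need not be balanced between arms. If the excluded children also differ in caries increment, the arm comparison shifts while the analysis still carries an intention-to-treat label. The article also intends to assess the feasibility and effectiveness of these applications in the field (Discussion). Outcomes in children who had significant events are part of that evidence.

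**Working it through.** **1. The two rules side by side**

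- Exclusion rule: triggered by a post-allocation event; the child leaves the trial; a note is made.
- Analysis rule: intention-to-treat, on change in dmfs over three years in a cohort recruited at ages 1 to 3.
- Outcome variables, Plan for analysis, and Data monitoring, quality assurance and auditing were checked for any statement that excluded children continue to be examined or remain in the analysis. There is none.

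**2. Is exposure to the rule likely to be equal?**

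- Group I: applications every 3 months over a three-year intervention phase, so 36 / 3 = 12 dentist contacts at most.
- Both groups: four post-baseline assessments (6 months, 1, 2 and 3 years).
- Group I therefore has both a source of events that Group II lacks and more occasions on which any event could be noticed. This is reasoning from the design. The article gives no adverse event rate for either arm.

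**3. The plan's own figure**

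Inputs from Sample size estimation: "the mean (SD) change of dmfs in intervention and control arm was 11 (14.3) and 13.47 (16.3), respectively", a difference of 2.47, 5% alpha and 20% beta.

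- n per arm = (z_0.975 + z_0.80)² × (14.3² + 16.3²) / 2.47²
- = 7.849 × (204.49 + 265.69) / 6.1009 = 604.9

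The stated 605 is reproduced. The target effect of 2.47 and the SDs can therefore serve as the scale for the bias. The finding disputes no figure in the sample size section.

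**4. Size of the bias**

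Let f be the share excluded in the intervention arm in excess of control, and D the gap in mean dmfs change between excluded and retained children. If a share f leaves, the retained mean equals the full-arm mean minus f × D, so bias = f × D. Both f and D are assumptions. D is run from 2.47 (the target effect) to 14.3 (one intervention-arm SD).

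| Excess excluded, f | D = 2.47 | D = 14.3 | Share of 2.47 |
|---|---|---|---|
| 1% | 0.02 | 0.14 | 1% to 6% |
| 5% | 0.12 | 0.72 | 5% to 29% |
| 10% | 0.25 | 1.43 | 10% to 58% |

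With D = 0 the bias is zero at every f. If the excluded children have the worse caries change, the intervention is flattered; if the better, it is penalised. The top of the range is realistic only in the first direction. With a reference mean of 11, a gap of 14.3 the other way would give excluded children a mean change of 11 − 14.3 = −3.3.

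**5. Effect on power**

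This uses the article's formula without clustering and 950 per arm at one centre.

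- No exclusions: SE = √(204.49/950 + 265.69/950) = 0.704; power 94.0%.
- 10% of the intervention arm excluded (855 v 950): SE = √(204.49/855 + 265.69/950) = 0.720; power 92.9%.

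These values show only the relative loss, which is small; the formula ignores clustering. What is at stake is bias, not precision.

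**The case against.** The strongest reply is that the sentence belongs to a safety and monitoring paragraph, does not mention the analysis set, and does not say that data already collected are discarded. A child can leave participation and still be analysed in the allocated arm, and the mixed models or generalised estimating equations allowed under Plan for analysis can use visits made before exclusion. The authors may have meant only that study applications stop. The article is also a condensed account, and a fuller document may define the analysis set.

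Part of this stands. A reader might infer that the two rules are flatly incompatible; the text supports only that they are unreconciled. But the sentence says the trial, not the applications, and adds nothing beyond a note. Visits before exclusion do not supply the three-year value, and a t-test on three-year change, also among the listed methods, could not include the child without it. This is a stated rule that needs correcting, not a detail left to another document.

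Other stronger readings are tempting and are not supported:

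- **That exclusions will fall mainly on the intervention arm.** The rule covers both arms, no rates are given, and the article does not say what counts as significant. Unequal loss is a reasonable expectation from the design, not an established fact.
- **That children are selected by their response to treatment.** An adverse event is not a caries response, and nothing in the article ties one to the other.
- **That later safety follow-up is hidden.** Events must be documented, reported and, where warranted, treated. What is unstated is whether observation continues afterwards.

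**Conclusion.** The concern holds as a failure to reconcile two stated rules. As written, one sentence ends three-year dmfs collection after a post-allocation event, while another promises an intention-to-treat analysis of that same outcome.

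The numerical consequence cannot be fixed from the documents, because the excess share excluded and the outcome gap are both assumed. It is negligible if exclusions are rare, at most about 0.14 surfaces at a 1% excess. It becomes material only if they are common, unequal and related to outcome, reaching about 0.72 surfaces at a 5% excess with a gap of a full SD. A reader might take the upper figures as the expected bias; the documents give no ground for that, and the direction is unknown. This should be fixed because the correction is simple and missed examinations cannot be recovered. It is not shown to invalidate the trial.

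**What to change.** Reconcile Data monitoring, quality assurance and auditing with Plan for analysis by separating a change in study treatment from leaving the trial. Replacement text could read:

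> A child who has a significant adverse event remains in the trial, attends all scheduled outcome examinations unless consent is withdrawn, and is analysed in the allocated arm. Any change in study treatment is recorded separately. Adverse events are reported by arm.

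Whether applications continue for such a child is a clinical decision that this point does not address.

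The edit is about one sentence, and 605 and 950 per arm are unchanged. The running cost is the effort of continuing to examine these children at the scheduled visits. The change should be made before any child is excluded under the present wording.
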